## Study Outcomes and Data Analysis

### Efficacy Outcomes

As we expect a short, 5-day course of tDCS to have a short-lasting effect on brain function, we will only assess short-term outcomes at 28 days after the end of tDCS.

The primary efficacy outcome will be the change in headache days from the 28-day baseline to the 28-day follow-up period.

The secondary outcomes will include the change in migraine days, headache hours, mean pain intensity (0–10 Visual Analog Scale), acute treatment consumption (doses), migraine-related disability (mMIDAS score) and impact (HIT-6 score), quality of life (SF-36 score), sleep quality (PSQI score), and anxious and depressive symptoms (HADS score) from the 28-day baseline to the 28-day follow-up period. The change in the number of days with low, medium, and high disability will also be assessed by using of a specifically designed headache diary (Supplementary Material 2).

The additional outcome will be the changes in spectral power and coherence in the delta (1–4 Hz), theta (5–7 Hz), alpha (8–12 Hz), and beta bands (13–30 Hz), both overall and over the occipital regions, at EEG recording between the two measurements (before vs. after tDCS). The EEG power changes will be correlated with the improvement in primary and secondary outcomes. The age limit of 40–70 years was chosen to limit the variability in EEG activity generated by the inclusion of too young or old subjects, which could act as a confounder in outcome assessment.

Each outcome will be assessed in the group of active and sham tDCS; additionally, between-group comparisons will be made.

A migraine day will be defined as a day with headache lasting at least 4 h if left untreated and accompanied by typical symptoms (nausea, vomiting, photo- and/or phonophobia) or preceded by aura. All days with headache not accompanied by any of those symptoms will be considered as non-migraine headache days. The total count of headache days will include both migraine and non-migraine headache days.

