### Statistical Analysis

Continuous data will be summarized by mean, standard deviation (SD), median, first and third quartiles, minimum and maximum, Categorical data will be presented by absolute and relative frequencies (n and %). Bilateral 95% confidence limit will be presented as appropriate.

Comparison between groups (active/sham) for the variables under study (headache days, days of disabling headache, intensity of pain, consumption of acute treatments, headache-related disability, and scores on questionnaires) will be performed using parametric or non-parametric statistics, depending on the data distribution.

Primary analyses will be performed on primary and secondary outcomes. Exploratory subgroup analyses will be performed on patients with a history of menstrual migraine and on patients with chronic migraine with medication overuse.

To evaluate electrophysiological changes, the dependent variable will be the variations in EEG activity after vs. before tDCS. Specifically, we will compute the spectral power *via* Fast Fourier Transform (FFT) and the coherence in cortical activity among brain areas via magnitude-squared coherence (MSC) for the artifact-free epochs in each EEG frequency band. For each group of patients (tDCS vs. sham), the power change before vs. after tDCS will be compared for each electrode and each frequency band. Given the results of a previous study (36), particular attention will be given to power in the alpha band in occipital areas. The EEG index changes will be correlated with changes in migraine parameters (headache days, migraine days, pain intensity, acute medication consumption, questionnaires score) to directly link the modifications in brain physiology to the frequency and severity of migraine episodes. Source current density of cortical generators of relevant EEG indexes will be also assessed by low-resolution electromagnetic tomography (LORETA) (37), to confirm the cortical origin of the physiological changes induced by tDCS. Outcomes will be compared between the active and sham tDCS groups by chi-squared or t-test statistics as appropriate.

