### Sample Size

The sample size calculation was performed using GPower, version 3.1. According to previous literature (36), a between-groups mean difference of 3 ± 2 migraine days per month was considered significant. The computation was made with the following parameters: confidence interval (two-sided): 95%; power: 80%; ratio of sample size: 1:1; mean change in group 1: −4 days; mean change in group 2: −1 day; standard deviation: 2. The minimum sample size suggested was of 9 patients per group. In consideration of possible dropouts, we set our population size to 30 patients, 15 per group.

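### The EEG–headache correlation is stated without a treatment-arm term; pooled over both arms, it can suggest a patient-level link too often when tDCS shifts both measures

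*Protocol article*

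**What the plan says.** The correlation is stated twice. Under Efficacy Outcomes: "The EEG power changes will be correlated with the improvement in primary and secondary outcomes". Under Statistical Analysis: "The EEG index changes will be correlated with changes in migraine parameters", with the listed parameters covering headache days, migraine days, pain intensity, acute medication and questionnaire scores. The second statement gives the purpose: "to directly link the modifications in brain physiology to the frequency and severity of migraine episodes".

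Neither sentence mentions treatment arm. Wording by group appears nearby, for other analyses. Efficacy Outcomes says "Each outcome will be assessed in the group of active and sham tDCS; additionally, between-group comparisons will be made". Statistical Analysis says of the EEG before/after comparison: "For each group of patients (tDCS vs. sham), the power change before vs. after tDCS will be compared for each electrode and each frequency band".

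The Sample Size section plans a clinical effect of "mean change in group 1: −4 days; mean change in group 2: −1 day; standard deviation: 2" and concludes "we set our population size to 30 patients, 15 per group". For the EEG, the Discussion reports that an earlier tDCS trial found higher occipital alpha power under active treatment. Statistical Analysis singles out occipital alpha for attention. No size for an EEG effect is given.

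**The concern.** The stated purpose is a claim about patients: that those whose EEG changes more are those whose migraine changes more. The relevant null hypothesis is no association between the two changes among patients given the same treatment.

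A correlation over both arms tests something else. Randomised arm is a common cause of both changes whenever tDCS moves both. The active arm then sits apart from the sham arm on both axes, and the gap between the two clusters alone produces a correlation. This affects even one correlation chosen in advance, so it is separate from the number of correlations planned. It arises in the scenario that the trial hopes for, with an effect on both headache and EEG.

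At stake is a mechanistic conclusion that could merely restate that tDCS shifted two averages. In the opposite case, with a clinical effect but no mean EEG shift, the arm difference acts as noise and can hide a real within-arm association.

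**Working it through.** **Inputs from the Protocol article.** Two-sided 5%, from "confidence interval (two-sided): 95%; power: 80%; ratio of sample size: 1:1"; 15 per arm; mean changes −4 and −1 days, SD 2. The standardised clinical effect is d_H = (4 − 1)/2 = 1.5. It comes from the migraine-day calculation, and migraine days are one of the correlated parameters.

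**Assumed.** EEG shift d_E from 0.5 to 1.5 SD; normal change scores with equal within-arm variance.

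**The plan's own figure.** A two-sample t-test at d = 1.5 (noncentral t) has power 0.797 with 8 per group and 0.848 with 9. The stated minimum of 9 is reproduced.

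**Correlation created by pooling.** With 1:1 allocation and zero within-arm correlation, the arm difference adds d_H·d_E/4 to the covariance and d²/4 to each variance (within-arm variance 1), so

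|ρ| = (d_H·d_E/4) / √[(1 + d_H²/4)(1 + d_E²/4)].

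For d_H = d_E = 1.5: 0.5625/1.5625 = 0.36. For d_E = 0.5: 0.1875/√(1.5625 × 1.0625) = 0.15.

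**Hand check.** With 30 patients (28 df, t = 2.048), the critical |r| is 2.048/√(28 + 2.048²) = 0.361. A pooled ρ of 0.36 sits on that boundary, so rejection in about half of trials is expected.

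**Simulated rejection rates.** 40,000 trials per row, 15 per arm, d_H = 1.5, no within-arm association:

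| Assumed EEG shift (SD) | Pooled ρ (absolute) | Pooled Pearson | Pooled Spearman | Adjusted for arm |
|---|---|---|---|---|
| 0 | 0 | 4.9% | 5.0% | 4.9% |
| 0.5 | 0.15 | 12.2% | 12.3% | 5.1% |
| 0.8 | 0.22 | 22.8% | 23.5% | 5.1% |
| 1.0 | 0.27 | 31.5% | 32.9% | 5.0% |
| 1.5 | 0.36 | 54.0% | 57.1% | 5.1% |

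The rank correlation does no better, so the non-parametric option described in the Discussion does not remove the problem.

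**Sensitivity.** With d_H = 0.5, pooled Pearson rejects in 6.3% to 11.8% for EEG shifts of 0.5 to 1.5 SD. If only one measure shifts, or neither, the rate is about 5%. With 9 per arm and d_H = 1.5, it is 9.0% to 33.7%.

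**Power when a link exists.** Take a true within-arm correlation of 0.5, d_H = 1.5 and no mean EEG shift. Pooling dilutes the correlation to 0.5/√1.5625 = 0.40. Power is about 60% pooled, 81% adjusted for arm (27 df), and 50% to 51% in a single arm of 15.

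**The case against.** The strongest reply is that the article never says the correlation is pooled. Method and handling of arm are details that an unseen analysis plan may supply, and the sentence on assessing each outcome by group follows directly after the paragraph that introduces the correlation. On a per-arm reading the error rate is nominal. This stands in part: a reader might infer that the plan fixes a pooled correlation, and it does not. But the by-group wording is attached to outcomes and to the before/after power comparison, not to the correlation, so pooling remains the more natural reading. The article also goes beyond leaving a detail open, because it states the conclusion that the correlation is meant to support. The per-arm reading has its own cost, power of about one half at r = 0.5, so the same change improves on either reading.

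A second reply is that the figures depend on an EEG shift that the protocol never plans, and that the Discussion allows for a negative clinical result. This also stands. A reader might infer that a false link is near certain under the protocol's own assumptions; the documents do not support that.

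A third reply is that adjusting for arm does not establish a direct link either. That is correct. A patient-level common cause could produce a within-arm association, and a single adjusted coefficient assumes a similar slope under active and sham stimulation. The Discussion's own description of EEG as a correlate of clinical findings is closer to what the data can show.

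**Conclusion.** The point holds in conditional form. If the correlation is run over both arms, and if active tDCS shifts both measures, it rejects too often with no within-arm association: about 12% to 54% at a nominal 5% for a clinical effect of 1.5 SD and assumed EEG shifts of 0.5 to 1.5 SD. The upper figure needs an EEG effect as large as the planned clinical one. Both conditions are required, and the excess is small if the clinical effect is small. If the analysis is run by arm, the weakness is lost power, not false rejection. On either reading, the direct-link wording claims more than a correlation can support.

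This concerns an additional, mechanistic analysis. The primary efficacy comparison and the sample size are not affected. The plan should be changed because the remedy costs little and the conclusion at risk is the trial's account of how tDCS acts.

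**What to change.** Under Statistical Analysis, specify a partial correlation given treatment arm (rank-based if the distributions require it) or, equivalently in the linear case, a regression of clinical change on EEG change with a term for arm. Make the sentence under Efficacy Outcomes agree. Base any statement of a link on that coefficient alone, and word it as a patient-level association. If an unadjusted correlation is shown, label it descriptive and say that it includes the difference between arms.

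The cost is one degree of freedom (27 instead of 28) and no new data. When tDCS moves both measures in the hoped-for direction, the adjusted coefficient will usually be smaller than the unadjusted one.

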### Sample Size

The sample size calculation was performed using GPower, version 3.1. According to previous literature (36), a between-groups mean difference of 3 ± 2 migraine days per month was considered significant. The computation was made with the following parameters: confidence interval (two-sided): 95%; power: 80%; ratio of sample size: 1:1; mean change in group 1: −4 days; mean change in group 2: −1 day; standard deviation: 2. The minimum sample size suggested was of 9 patients per group. In consideration of possible dropouts, we set our population size to 30 patients, 15 per group.

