We will also study the cortical effect of neuromodulation by electrophysiology (EEG). Previous studies have shown that EEG activity is different between subjects with and without migraine. In detail, migraineurs showed increased slow activity between attacks compared with non-migraineurs (51, 52) and the degree of EEG slowing on the occipital areas showed a correlation with the burden of migraine (53); the increase in slow activity is coupled with decreased power of the alpha frequency. Interestingly, a trial of anodal tDCS over the frontal motor areas showed that active treatment was associated with increased alpha power over the occipital regions (36), suggesting that tDCS can mitigate the neurophysiological abnormalities of the migraineurs' brain. Quantifying EEG activity in our trial will provide a neurophysiological correlate to clinical findings and will help explaining the effect of tDCS on neural structures. The use of high-density EEG will provide accurate information on the sites of tDCS action.

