The present trial has a robust double-blind, randomized approach with blinded outcome assessment. The trial complies with the most recent guidelines for neuromodulation in migraine. Besides, the tDCS montage was designed specifically for migraine prevention by reflection on the most plausible neuroanatomical targets. However, the study also has limitations. The study is single-center; besides, its sample will be sufficient to calculate the primary outcome, while subgroup analyses will be only exploratory. We will correct for low numbers by assessing the normality of variable distributions and perform conservative, non-parametric tests for non-normally distributed variables. As an add-on to highly effective migraine preventatives, we cannot exclude that the clinical effect of tDCS in the present RCT will be negative. Nevertheless, we will include patients with a high burden of migraine (≥8 monthly migraine days) to correct for this effect. Besides, a previous trial showed that active tDCS is more effective than sham even on top of topiramate (47), suggesting that tDCS could be an effective add-on migraine preventative. Besides, we will assess not only the possible clinical efficacy of tDCS, but also its effect on brain circuitry; therefore, even results that are clinically neutral will be interesting to discuss with respect to the functional effects of tDCS. Our trial will contribute to assess the possible central, indirect effects of CGRP-MAbs by verifying whether the central circuits of migraine generation can be inhibited in addition to the action of those drugs.

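### The sample size is calculated for migraine days, a secondary outcome; power for the primary outcome, headache days, is undetermined, so the claim that the sample is sufficient for it is unsupported

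*Protocol article*

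**What the plan says.** Under Efficacy Outcomes the primary variable is explicit: "The primary efficacy outcome will be the change in headache days from the 28-day baseline to the 28-day follow-up period". Migraine days come first in the next list: "The secondary outcomes will include the change in migraine days, headache hours, mean pain intensity (0–10 Visual Analog Scale". The same section makes clear that these are two different counts: "The total count of headache days will include both migraine and non-migraine headache days".

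The Sample Size section then takes its effect from a single cited study and names the variable: "a between-groups mean difference of 3 ± 2 migraine days per month was considered significant". The parameters entered in the software follow from it: "mean change in group 1: −4 days", against a change of −1 day in the other group, with an SD of 2, a two-sided 95% confidence level, 80% power and 1:1 allocation. The result is 9 per group, raised to 15 per group to allow for dropouts.

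The Discussion, listing the limitations, draws a conclusion about the primary outcome: "its sample will be sufficient to calculate the primary outcome, while subgroup analyses will be only exploratory".

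**The concern.** The calculation and the conclusion drawn from it concern different variables. A headache-day count adds days that the migraine-day count leaves out. Its mean change, its SD and the difference between arms may therefore all differ from those of migraine days. The article gives none of these quantities for headache days and nowhere says that the migraine-day values are meant to stand in for them.

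What is at stake is how far the power statement can be relied on. With 30 patients, power depends heavily on the SD of the change. A reader of the Discussion would take it that the primary comparison has at least 80% power, when the document supports that only for a secondary outcome.

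Shortening for publication does not explain this. The article gives the calculation in full and names its variable, and a separate analysis plan would not make the Sample Size section and the Discussion agree.

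**Working it through.** **Inputs from the Sample Size section (migraine days).** Mean changes −4 and −1, so the difference is 3; SD 2; two-sided α = 0.05; power 80%; ratio 1:1. The standardised difference is d = 3/2 = 1.5.

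**Reproducing the plan's figure.** For a two-sample t-test, power comes from the noncentral t distribution with 2n − 2 degrees of freedom and noncentrality d·√(n/2).

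- n = 8 per group: noncentrality 1.5 × √4 = 3.00, power 79.7%.
- n = 9 per group: 1.5 × √4.5 = 3.18, power 84.8%.
- n = 15 per group: 1.5 × √7.5 = 4.11, power 97.7%.

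The smallest n that reaches 80% is 9, as stated. The Statistical Analysis section allows a non-parametric test, but this changes little. With a Wilcoxon test the answer is 9 per group for normal data (relative efficiency 3/π) and 10 in the least favourable case (0.864).

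**Setting the variables side by side.**

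| | Variable | Difference given | SD given |
|---|---|---|---|
| Sample Size | migraine days (secondary) | 3 | 2 |
| Efficacy Outcomes | headache days (primary) | none | none |
| Discussion, sufficiency claim | primary outcome | none | none |

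**What 15 per group gives for headache days.** The article offers no inputs, so the differences and SDs below are assumptions, and no single corrected figure is possible. The test is the same t-test at two-sided 5%. Each cell shows power at 15 per group, with the number per group needed for 80% in brackets.

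| Assumed difference | SD 2 | SD 3 | SD 4 | SD 5 |
|---|---|---|---|---|
| 3 days | 97.7% (9) | 75.3% (17) | 50.9% (29) | 35.5% (45) |
| 2.5 days | 91.0% (12) | 59.6% (24) | 38.0% (42) | 26.2% (64) |
| 2 days | 75.3% (17) | 42.2% (37) | 26.2% (64) | 18.5% (100) |

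**Limits at 15 per group.** Solving for 80% power at SD 2 gives a difference of 2.12 days, so the detectable standardised difference is 2.12/2 = 1.06. From this:

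- Detectable difference = 1.06 × SD: 2.1, 3.2, 4.2 and 5.3 days at SD 2, 3, 4 and 5.
- Largest SD at which a 3-day difference keeps 80% power: 3/1.06 ≈ 2.83.

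**The case against.** The strongest reply is that 15 per group leaves a wide margin and that the two counts may be close. Both parts have some force. If the migraine-day values carry over, power is about 98%, and a 3-day difference keeps 80% power up to an SD of about 2.83. The Study Discontinuation section recruits until 15 patients per arm have completed, replacing losses within the 12-month inclusion period, so 15 is a fair number to use. The eligibility criteria also restrict other primary headache types to less than one day a month, which narrows the gap between the counts. It does not close it: any headache day without the listed accompanying symptoms counts as a non-migraine headache day, and the article keeps the two outcomes apart. The margin holds only if the values transfer, and the article neither says nor argues that they do.

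A reader might also infer stronger things, which the documents do not support.

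- *The trial is underpowered, or could detect only a very large effect.* That depends on the SD of change in headache days, which is unknown here.
- *An SD of 2 is implausible.* One could treat days as independent, so that counting noise alone gives a change SD of √(2 × 28 × p(1 − p)), which is 3.4 at 8 days in 28 and 3.7 at 12. Nothing in the article supports independence, and the same formula gives only 1.9 at 26 days in 28. The source of the SD of 2 is a cited study that is not at hand.
- *The effect comes from an unrelated setting.* The Discussion says of the cited study that "a trial of anodal tDCS over the frontal motor areas showed that active treatment was associated with increased alpha power". The present montage also places anodes over the motor areas and adds occipital cathodes, and borrowing an effect from a related trial is ordinary practice.
- *The article concedes that there may be no effect.* It does say "As an add-on to highly effective migraine preventatives, we cannot exclude that the clinical effect of tDCS in the present RCT will be negative", but that caution does not conflict with sizing a trial for an assumed effect.

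**Conclusion.** The point stands in a limited form. The sample size calculation is arithmetically right but is made for a secondary outcome. For the primary outcome the power is undetermined, and the Discussion's sufficiency statement is unsupported. This is a mismatch between endpoint and power calculation. It is neither a calculation error nor evidence that 30 patients are too few.

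Its possible size is wide. Over assumed differences of 2 to 3 days and SDs of 2 to 5 days, power at 15 per group runs from about 19% to 98%. The article gives no basis for placing headache days within that range. The mismatch itself rests on no assumption, since it is in the text; the range rests on the assumed differences and SDs and on a two-sample t-test with 15 completers per arm.

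The power statement should be corrected, but the point does not put the design in doubt.

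**What to change.** 1. Restate the calculation for the change in headache days over 28 days, giving the expected difference and SD and their source. Alternatively, state that the migraine-day values are being carried over and say why that is reasonable. If they are kept, note that the calculation is expressed per month while the outcome covers 28 days.
2. Report power, or the difference detectable with 80% power, at 15 per group over a stated range of assumed SDs. The 3-day row and the detectable differences in the working would serve.
3. Qualify the Discussion sentence so that it claims sufficiency only under the stated difference and SD for headache days.

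This means new figures and a few reworded sentences, with no change to enrolment or trial conduct. The only cost is that the stated power may become less favourable.
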